**Statistical analysis**

Continuous data will be summarized as mean ± standard deviation, and compared among groups with student t test or Wilxocon’s rank sum test as appropriate. Discrete data will be summarized as number (%) and compared by chi square or Fisher’s exact test as appropriate. All statistical tests are two tailed, considered significant with p value < 0.05 Survival analysis will be visually presented by Kaplan Meier’s Curve, and compared by hazard ratio. Statistical software SPSS 24.0 will be used.

Crude 30 and 90-days survival distributions between treatment [TPE] and control [no TPE] groups will be described using proportions and Kaplan Meier distributions. Crude differences will be tested using Chi Square test [for proportions] and a log-rank test [for the Kaplan Meier survival distributions]. A multivariable analysis of the primary 30 and 90-days survival outcome will be conducted using a Cox Proportional Hazard model where the main effect of treatment [TPE versus no TPE] and relevant confounding variables: age, gender, admission PaO2/FIO2 ratio, admission APACHE II and SOFA scores, presence of acquired coagulopathy and high vs low CRS group (already defined in previous paragraphs) will be entered into the model a-priori.

Similarly, a logistic regression multivariable model including the aforementioned variables will be fit to determine the independent effect of the TPE treatment on the binary outcome of 30 and 90 days survival.

Daily whole blood and effluent plasma samples will be obtained and assayed for various inflammatory markers IL-6, C-RP, ferritin etc. General estimating equations using random effects models will be used to describe the temporal changes in whole blood [in both treatment and control groups] and effluent plasma [in TPE group only]. Standard comparisons of the change in inflammatory markers using robust variance estimators will be used to compare the changes in these markers between treatment and control group.

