**Timeline**

The recruitment phase will extend over a period of 6 months aiming on including at least 20 patients in the study group (TPE) and 20 controls (patients with severe COVID-19 who will undergo standard therapy per MOH, KSA protocol and who will provide consent only to share their clinical and laboratory data) per participating center. Starting date: 10-05-20.

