**Study design**

We are aiming on a pilot prospective design of 6 months duration. We are aiming to include at least 20 adult patients with severe COVID-19 as per inclusion criteria in our study group (TPE arm) per participating center. At least 20 COVID-19 patients and/or their next of Kin who will only consent for sharing their clinical and laboratory data (they will be treated per standard MOH protocol) will serve as a control group to compare the efficacy of the intervention per participating center. Our primary specific aim of this pilot randomized controlled trial is to evaluate the safety of utilizing TPE in critically ill COVID-19 patients and 28 day mortality. At present our best estimate of this critically ill population's mortality is 50%. As COVID-19 is a novel virus and the global pandemic interventions will result in dynamic changes in incident rates of this infection, we will be enrolling a convenience of critically ill COVID-19 patients in order to inform us of an estimated mortality rate and variability of organ dysfunction in order to inform the sample size calculation of a definitive randomized controlled trial in the future. Consequently we are hoping to consent and randomize approximately 60 patients in each group over a 3 to 6 months period. The two groups will be receiving the same standard mechanical ventilation protocols (i.e., proning, ventilation strategies) as per hospital protocol. Antibiotics, antivirals, other medications and dialysis/CRRT will be applied between groups as per hospital and Saudi MOH protocols for treatment of patients with serious COVID-19 (Saudi Ministry of Health. Coronavirus Diseases 19 (COVID-19) guidelines. March 2020; version 1.2; (https://covid19.moh.gov.sa).

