**Secondary endpoints:**

Improvement of organ function as evaluated per SOFA score

Changes in laboratory inflammation markers

ICU length of stay

Number of days on mechanical ventilation

**Randomization** Eligible consented patients will be randomized after their stratification by ICU center and two PaO2/FIO2 ratio categories (> 150 and ≤ 150). Randomization will occur in variable block sizes of 4 to 8 patients. We will utilize a web-based randomization service, [randomize.net](http://randomize.net/) to allocate patients to their respective strata prior to the intervention or control therapy. Given the nature of the TPE technology, the intervention will be unblinded (open label); hence, no enrollment concealment will be expedited. However, the lack of allocation concealment will be mitigated as much as possible by the following measures. First, the primary outcome of mortality will not be disputable. Second, we have standardized co-interventions that impact on mortality as much as possible. These interventions include a) concomitant drug therapies for COVID-19, b) algorithms for mechanical ventilation including the early use of prone-ventilation, low tidal volume ventilation and neuromuscular blockade, c) the standard use of a broad spectrum antibiotic(s) for a minimum of 7 days to treat any potential superinfection be a bacterial pneumonia and d) standard criteria to initiate intermittent hemodialysis or CRRT such as hyperkalemia, profound metabolic acidosis, oliguria unresponsive to furosemide challenges of 1-1.5 mg/kg, e) the presence or development of coagulopathy defined as INR > 3.0 or Fibrinogen < 1.0 will be treated in a standard fashion in both the intervention and control group. We will define the date/time of appropriateness for ICU transfer irrespective of treatment allocation and recognizing that some COVID-19 patients randomized to the intervention group may improve to the point of appropriateness to transfer to the medical ward but requiring ICU care only to deliver remaining TPE doses as outlined in the protocol.

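### Raw ICU stay and ventilator days are compared with no account of death, so at an expected 50% mortality the comparison mixes survival with duration

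*Protocol*

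**What the plan says.** The Secondary endpoints section of the protocol lists four items: SOFA improvement, change in inflammatory markers, length of ICU stay, and "Number of days on mechanical ventilation". The last two are raw durations.

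The Statistical analysis section has one rule for continuous data: "Continuous data will be summarized as mean ± standard deviation, and compared among groups with student t test", or a Wilcoxon rank-sum test where appropriate. Kaplan-Meier, log-rank, Cox and logistic methods are given for survival only. For the daily markers it says "General estimating equations using random effects models will be used to describe the temporal changes in whole blood", with a between-arm comparison of change using robust variance.

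The Study design section states "our best estimate of this critically ill population's mortality is 50" per cent, and gives the size as follows: "Consequently we are hoping to consent and randomize approximately 60 patients in each group over a 3 to 6 months period".

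No section defines ICU-free or ventilator-free days, gives a death a value or a rank, or names a competing-risk or joint method. The Randomization paragraph does protect ICU stay in one respect. It sets a date of readiness for transfer, so that a patient kept in ICU only to finish TPE sessions is not counted as needing ICU. That does not deal with death.

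**The concern.** Under these rules a patient who dies on day 2 contributes a two-day ICU stay and few ventilator days. Those values score better than those of a survivor who leaves on day 16. Using the rank-sum test instead of the t test does not help, because early deaths still take the favourable ranks. With half the patients expected to die, the comparison of durations is partly a comparison of mortality, and it may run in the opposite direction to mortality. At stake is whether two of the four secondary endpoints can be read as evidence about recovery. The pilot is also meant to inform a definitive trial, so a misread duration could carry over into that design.

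The other two endpoints have a related, weaker problem. SOFA and marker series are cut short by death and by discharge, and the plan has no rule for either. The marker sentence also joins two methods: generalized estimating equations are marginal and have no random effects, while random-effects models are subject-specific. The two make different assumptions about missing values, so the text does not settle which analysis will be run.

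**Working it through.** The protocol gives no calculation for these endpoints, and no effect size or power for any endpoint, so there is no figure to reproduce.

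**Inputs from the protocol:** mortality 50%, applied here to the control arm because it is not given by arm; about 60 patients per arm; two-sided 0.05.

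**Assumed, because the protocol gives neither:** TPE mortality of 40% or 30%; mean ICU stays for survivors (S) and non-survivors (D). TPE is taken to change mortality only.

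**Raw stay.** With mortality m, the mean stay in an arm is (1 − m) × S + m × D. Subtracting control from TPE gives

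shift = (m_control − m_TPE) × (S − D).

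| S / D (days) | Control, 50% | TPE, 40% | TPE, 30% | Shift (days) |
|---|---|---|---|---|
| 20 / 10 | 0.5×20 + 0.5×10 = 15.0 | 0.6×20 + 0.4×10 = 16.0 | 0.7×20 + 0.3×10 = 17.0 | +1.0, +2.0 |
| 15 / 10 | 12.5 | 13.0 | 13.5 | +0.5, +1.0 |
| 15 / 15 | 15.0 | 15.0 | 15.0 | 0, 0 |
| 10 / 15 | 12.5 | 0.6×10 + 0.4×15 = 12.0 | 0.7×10 + 0.3×15 = 11.5 | −0.5, −1.0 |

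A positive shift makes the life-saving arm look worse. The sign is that of S − D, which the protocol does not give.

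**How often it would show.** This was checked with 4,000 simulated trials per case, 60 per arm, and gamma-distributed stays of shape 2. In the 20/10 case TPE has the longer mean stay in 68% of trials at 40% mortality and 80% at 30%. It is significantly longer in 6.0% and 13.6% by t test, and in 6.5% and 14.7% by rank sum. With no mortality difference the t-test figure is 2.5%. In the 10/15 case TPE has the longer mean in only 38% and 27% of trials.

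**Free days to day 28, death = 0.** Deaths contribute nothing, so the difference is (m_control − m_TPE) × (mean free days among survivors). If TPE changes mortality only, this cannot point against the arm with fewer deaths. Simulated mean differences in favour of TPE, in days:

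| S / D (days) | 50% vs 40% | 50% vs 30% |
|---|---|---|
| 20 / 10 | +1.09 | +2.15 |
| 15 / 10 | +1.41 | +2.81 |
| 15 / 15 | +1.42 | +2.83 |
| 10 / 15 | +1.79 | +3.65 |

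The sign is stable across all four stay patterns, unlike that of raw stay. Days of ventilation follow the same algebra.

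**The case against.** The direction is not established. A reader might infer that a mortality benefit will appear as a longer ICU stay, but the documents do not support that. It needs non-survivors to leave ICU sooner than survivors, and the protocol gives no stay data. It also needs TPE to leave survivors' stay unchanged. Take assumed stays of 16 and 8 days and mortality of 50% against 35%. If TPE also cuts survivors' stay to 14 days, the means are 0.5×16 + 0.5×8 = 12.0 and 0.65×14 + 0.35×8 = 11.9, so the apparent harm disappears. This stands and limits the claim to what can happen. The same example shows the other side: a treatment that improves both survival and survivors' stay would show almost no difference.

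The share of significant results depends on the assumed spread of stays. For the 16/8 case at 50% against 35%, with TPE changing mortality only, the significant share is 6%, 10% and 21% for gamma shapes 1, 2 and 9, and 38% with no spread at all. The mean shift does not depend on the spread.

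A reader might also infer that SOFA is seen only in survivors, or that all four secondary endpoints lean against TPE. Neither follows. The Data collection section schedules SOFA on days 3 and 7, and the Response assessment section lists it daily, so patients who die later still contribute early scores. For SOFA and the markers the bias has no fixed direction. One reading of the marker sentence is already a mixed model, so that part is a request for clearer wording.

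Finally, these are secondary endpoints of a pilot, mortality will be reported beside them, and an analysis plan that is not shown may add detail. That lowers the weight of the point but does not remove it. The form of the two endpoints and the tests for continuous data are both written in the protocol, and together they count an early death as a good result.

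**Conclusion.** The point holds in this form: ICU stay and ventilator days, as defined and tested, mix survival with duration at the protocol's own expected mortality of 50%. If TPE changes mortality only, and mortality falls from 50% to 40% or 30%, the shift in mean ICU stay is +1.0 to +2.0 days against TPE for stays of 20/10 days (survivors/deaths), zero for equal stays, and −0.5 to −1.0 days for 10/15. A life-saving effect can look like a longer stay. At 60 per arm that would seldom be significant: about 6–14% of trials by t test in the 20/10 case with the assumed spread. All stay lengths and TPE mortalities are assumptions.

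SOFA truncation and the merged marker method are secondary points with no stated size or direction. The 28-day mortality endpoint is unaffected. The change should be made, but it is not critical to the trial's main question.

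**What to change.** Replace the two durations with ICU-free and ventilator-free days to day 28, compared by Wilcoxon. Score death by day 28 as 0 or as the worst rank, and say which: with 0, deaths tie with survivors still in ICU or still ventilated at day 28. State whether ICU stay ends on the transfer-readiness date in the Randomization paragraph or on the actual transfer date. Beside the result, show mortality and the raw durations by survival status, descriptively.

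Compare SOFA at one scheduled early day (for example day 3 or day 7), with deaths ranked worst and a stated rule for patients already discharged. For the markers, name one method, for example a linear mixed model on log-transformed values. Interpret it alongside deaths, because such a model carries trajectories past death.

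**Cost.** The free-day endpoints redefine two secondary endpoints but use data the protocol already collects. The SOFA rule may call for a score at or near discharge. The small downside is that free days combine death and duration, which is why the components must be shown with them.

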**Data collection**

Clinical information of all enrolled cases will be retrieved from the hospital electronic/paper records system, including the: baseline demographic data, days of illness duration, presenting symptoms, radiological findings (CXR and Chest CT scans when possible), Sequential Organ Function Assessment (SOFA) and APACHE II scores. Data will be collected upon hospital/ICU admission, and prior to the first TPE session (Day 0) then on days 3, 7, 14, 30 accordingly and/or upon ICU/hospital discharge. Laboratory infectious marker testing results like culture from respiratory, urinary or blood culture will be collected accordingly.

Common laboratory and inflammatory markers (see below) will be collected on a daily basis:

1. CBC differential to include percent and absolute lymphocyte count and percent and absolute neutrophil count

2. Chemistry panel to include Total protein, Albumin, Lactate Dehydrogenase (LDH), Aminotransferases (ALT, AST), Procalcitonin

3. Cardiac biomarkers (e.g. cardiac troponins)

4. CK

5. Ferritin, LDH

6. Full coagulation profile to include PT, APTT, fibrinogen and D-dimer levels

7. C Reactive Protein (CRP) and erythrocyte sedimentation rate (ESR)

8. Interleukin-6

RT-PCR test for SARS-CoV-2 will be done and will be monitored during treatment and at day 14 of recovery or discharge, whatever is later. Also, we will be monitoring: mechanical ventilation (MV) and modes, intranasal oxygen inhalation, non-invasive mechanical ventilation, number of days of MV or nasal oxygen support, medication regimens (i.e., hydroxychloroquine, anti-viral therapies, steroids, tocilizumab, etc.), complications (including acute renal failure, acute coronary syndrome, myocarditis, acute respiratory distress syndrome, GI complications, CNS complications and nosocomial infections).

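### The SOFA endpoint falls under an unadjusted t or rank-sum rule although admission SOFA is in hand; adjusting for it would gain precision, by an amount the protocol does not allow one to fix

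*Protocol*

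**What the plan says.** The protocol lists as its first secondary endpoint "Improvement of organ function as evaluated per SOFA score" (Secondary endpoints). It names no day and does not say whether improvement means a change, a follow-up score or a yes/no response.

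The Statistical analysis section has no sentence on SOFA as an outcome. A continuous SOFA measure therefore falls under the general rule: "Continuous data will be summarized as mean ± standard deviation, and compared among groups with student t test or Wilxocon’s rank sum test as appropriate". Testing is at the usual level: "All statistical tests are two tailed, considered significant with p value < 0.05". The same section enters admission SOFA as a covariate in the Cox and logistic models for survival. It gives a longitudinal model for inflammatory markers only.

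Under Data collection, "Clinical information of all enrolled cases will be retrieved from the hospital electronic/paper records system", and the items listed there include SOFA. On timing: "Data will be collected upon hospital/ICU admission, and prior to the first TPE session (Day 0) then on days 3, 7, 14, 30". SOFA is also part of the daily clinical assessment (Response assessment).

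The Study design section sets the size, "Consequently we are hoping to consent and randomize approximately 60 patients in each group over a 3 to 6 months period". It gives the pilot a second job: patients are enrolled "in order to inform us of an estimated mortality rate and variability of organ dysfunction in order to inform the sample size calculation" of a later definitive trial.

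**The concern.** A patient's SOFA on a later day depends partly on how ill that patient was at the start. A plain two-sample test leaves that predictable part in the error term. The protocol recognises admission SOFA as prognostic when it models survival, yet makes no use of it for the endpoint it should predict most directly.

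Two things are at stake. The organ-function comparison is less precise than the collected data allow. And if the pilot hands on only a mean and SD, the team sizing the definitive trial lacks the two quantities needed to plan a baseline-adjusted analysis: the residual SD and the baseline-to-follow-up correlation.

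**Working it through.** **Inputs from the protocol.** Two-sided 0.05; about 60 per group, read as 1:1; expected mortality 50%. No power, effect size, SD or correlation is given for SOFA, and the 60 per group has no stated derivation, so there is no figure to reproduce.

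**Assumptions.** rho is 0.3, 0.5 or 0.7; baseline and follow-up variances are equal and set to 1; scores are normal and available on everyone.

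**Variances.**
- Follow-up score: 1
- Change score: 2(1-rho)
- Adjusted for baseline: 1-rho²

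The adjusted variance is therefore (1-rho²)/[2(1-rho)] = (1+rho)/2 of the change-score variance, and 1-rho² of the follow-up-score variance. The direction does not need equal variances. With baseline SD s0 and follow-up SD s1, the change-score variance minus the adjusted variance is (s0 - rho·s1)², which is never negative.

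**Power after adjustment, starting from 80%.** Power = Phi[(1.960+0.842)/√ratio - 1.960]. At rho 0.5 the ratio is 0.75 on either reading: 2.802/0.866 - 1.960 = 1.276, so power is 0.899. For a follow-up score at rho 0.7: 2.802/0.714 - 1.960 = 1.964, so power is 0.975.

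| rho | Ratio, change score | Power | Ratio, follow-up score | Power |
|---|---|---|---|---|
| 0.3 | 0.65 | 93.5% | 0.91 | 83.6% |
| 0.5 | 0.75 | 89.9% | 0.75 | 89.9% |
| 0.7 | 0.85 | 86.0% | 0.51 | 97.5% |

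Adjustment gains in every row, but the pattern reverses with the form of the endpoint. It helps a change score most when rho is low and a follow-up score most when rho is high.

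**The same check at a fixed effect.** Assume an effect of 0.5 raw SD. Figures are in the order follow-up / change / adjusted.

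| rho | Power, 60 per arm | N per arm for 80% power |
|---|---|---|
| 0.3 | 78% / 64% / 82% | 63 / 88 / 58 |
| 0.5 | 78% / 78% / 88% | 63 / 63 / 48 |
| 0.7 | 78% / 94% / 97% | 63 / 38 / 33 |

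A simulation of 10,000 trials at rho 0.5 agreed: 77% for t on follow-up, 78% for t on change, 76% for rank-sum on change and 88% adjusted. At rho 0.8 the gain over a change score is negligible at this effect (99.1% to 99.5%).

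**Passing the SD to the definitive trial.** At rho 0.5 the raw SD is 1/√0.75 = 1.15 times the residual SD. A trial sized on it would take 63 rather than 48 per arm, 31% more (63/48 = 1.31). This excess arises only if that trial is analysed with baseline adjustment.

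**Deaths.** If about half the patients had no follow-up SOFA, some 30 per arm would remain. At rho 0.5 and 0.5 SD, power would be 49% unadjusted against 61% adjusted. This shows scale only, since a survivors-only comparison is no longer the randomised one.

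**The case against.** The strongest objection is that this is a matter for the SAP. The sentence is a general rule that never names SOFA, adjustment of a secondary endpoint is commonly settled later, and the unadjusted test is valid. That limits the weight of the point but does not remove it: the protocol does state a method for continuous outcomes, offers no other for SOFA, and already holds the covariate.

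Four stronger readings are tempting and are not supported:
- **That the comparison is biased.** A change score over-corrects a chance baseline imbalance, whose SD is √(2/60) = 0.18 SD at 60 per arm, but across randomisations it is unbiased. Repeating this with 20 per arm would misread the protocol, where 20 is a minimum per group per centre.
- **That the pilot will hand over too large a variability figure.** The protocol does not say which SD it will pass on or how the definitive trial will be analysed. The raw SD is the right input for an unadjusted trial, and the residual SD and correlation can be computed later from the same data.
- **That a particular gain is assured, such as five points or more up to rho 0.7.** For a follow-up score at rho 0.3 it is under four points.
- **That the formulas describe this population.** They assume a score on everyone. With many deaths, and especially with a worst score assigned to the dead, the variance and correlation change, and a rank method may suit better than a linear model.

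If improvement were analysed as yes/no, the chi-square or Fisher rule would apply instead. Adjusting for admission SOFA would then need a different model, and the figures above would not carry over.

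**Conclusion.** The point holds as an inexpensive improvement, not as an error. For a continuous SOFA endpoint the stated test is valid but less precise than a baseline-adjusted comparison, whether improvement is a change (any rho below 1) or a follow-up score (any rho above 0). From 80% power, adjustment would give 86% to 94% for a change score and 84% to 97.5% for a follow-up score over rho 0.3 to 0.7.

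Those figures rest on an assumed correlation, an assumed endpoint form, an assumed starting power and complete follow-up; none comes from the protocol. With 50% mortality expected, the actual gain is uncertain. How deaths and the unnamed time point are handled is a separate and probably larger matter for this endpoint. The variability figure is too large only for a definitive trial that adjusts for baseline.

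**What to change.** In the Statistical analysis section, state that SOFA at one named day is compared by a linear model with treatment, pre-randomisation SOFA and the stratification factors (PaO2/FIO2 category and centre). Take the admission value as baseline: Day 0 is tied to a first TPE session that controls do not have. If deaths are given a worst score, use a baseline-adjusted rank or ordinal version of the comparison.

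Report the residual SD and the baseline-to-follow-up correlation beside the raw SD, so that the definitive trial can be sized for either kind of analysis.

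The cost is a few sentences, plus a decision on the day and on how deaths enter. The data are already collected, the linear model runs in the software already named, and no extra patients or visits are needed.

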**Study endpoint and outcome measures**

**Primary endpoints:**

28 day mortality and safety of TPE

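### The protocol declares 28-day mortality primary, but its statistical section calls 30- and 90-day survival primary and does not say which time point or test leads

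*Protocol*

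**What the plan says.** The endpoint section lists the primary endpoints as "28 day mortality and safety of TPE". Study design gives the primary aim in the same terms, to "evaluate the safety of utilizing TPE in critically ill COVID-19 patients and 28 day mortality". The Abstract and Research aim also name 28-day mortality.

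The Statistical analysis section uses other time points:

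- Crude comparison: "Crude 30 and 90-days survival distributions between treatment [TPE] and control [no TPE] groups will be described using proportions and Kaplan Meier distributions". Then: "Crude differences will be tested using Chi Square test [for proportions] and a log-rank test", the latter for the Kaplan-Meier curves.
- Adjusted time-to-event: "A multivariable analysis of the primary 30 and 90-days survival outcome will be conducted using a Cox Proportional Hazard model". Seven baseline covariates are fixed in advance.
- Adjusted binary: a logistic model with the same covariates for the "independent effect of the TPE treatment on the binary outcome of 30 and 90 days survival".
- Threshold: "All statistical tests are two tailed, considered significant with p value < 0.05".

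The section also opens with a general rule that discrete variables are given as counts and percentages and compared by chi-square or Fisher's exact test. That rule names no variable and no day.

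Under Data collection, the numbered days after Day 0 are 3, 7, 14 and 30, with ICU or hospital discharge as an addition or alternative. Neither day 28 nor day 90 appears.

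**The concern.** A trial should have one answer to the question of what its primary result is. Here the endpoint section and the statistical section answer differently. An analyst who follows the statistical section would report, as primary, survival at time points the trial did not declare.

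The statistical section does not settle the matter within itself either. It gives two time points and four methods, holds every test to the same 0.05, and states no order. If the results disagree, for example a significant adjusted Cox result to day 90 beside a non-significant chi-square at day 30, nothing in the protocol says which one counts. The lead result could then be picked with the data in view, and the stated 5% error rate would not describe it.

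**Working it through.** **1. The labels side by side**

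| Place in the protocol | Time point | Called primary or stated as the aim? |
|---|---|---|
| Abstract; Research aim | 28 days | yes, aim |
| Study design | 28 days | yes, primary aim |
| Study endpoint and outcome measures | 28 days | yes, primary endpoint |
| Statistical analysis, Cox sentence | 30 and 90 days | yes, primary outcome |
| Statistical analysis, chi-square, log-rank, logistic | 30 and 90 days | no label |
| Data collection | day 30 is the last numbered day | not applicable |

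**2. How many tests**

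- Widest reading, every method at each time point: 2 × 4 = 8.
- Narrower reading, log-rank and Cox each run once over follow-up: 2 (chi-square) + 2 (logistic) + 1 + 1 = 6.

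The text does not say which reading is meant.

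**3. What the count does to the error rate**

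The only stated error rate is the per-test 0.05. If eight tests were independent, the chance of at least one false positive would be 1 − 0.95^8 = 0.337; the sum of the eight levels is 8 × 0.05 = 0.40. Neither figure applies, because the tests reuse the same deaths and are strongly correlated. The joint rate has to be simulated.

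Inputs from the protocol: about 60 per group, 50% mortality (Study design attaches no day to it), seven covariates, two-sided 0.05. Assumptions, because the protocol gives no figures: the 50% is placed at day 28; survival times are Weibull; the covariates are four continuous and three binary, with a fixed set of log hazard ratios multiplied by the strength shown; there is no loss to follow-up and no treatment effect. There were 2,000 simulated trials per scenario.

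| Weibull shape | Covariate strength | Dead by day 28 / 30 / 90 | Any of 8 | Any of 4 at day 30 | Any of 4 at day 90 | Day-28 chi-square alone |
|---|---|---|---|---|---|---|
| 0.35 | 0.3 | 50.0 / 50.8 / 63.4% | 13.9% | 9.0% | 9.8% | 4.8% |
| 0.7 | 0 | 50.0 / 51.7 / 79.1% | 14.3% | 7.9% | 10.5% | 5.2% |
| 0.5 | 0.5 | 50.0 / 51.0 / 66.8% | 16.9% | 9.9% | 12.4% | 5.0% |
| 0.5 | 1 | 50.0 / 50.7 / 61.8% | 18.5% | 12.0% | 13.7% | 5.2% |

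The Monte Carlo standard error for a rate near 15% is √(0.15 × 0.85 / 2000) = 0.008. A separate simulation of 1,500 trials, with about 50% dead by day 30 and 59% by day 90, gave 15.3% for any of eight and 10.9% within day 30. With 57% and 66% dead it gave 16.5% and 11.6%.

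The six-test reading was not simulated. If the single log-rank and Cox tests run to day 90, the six contain all four day-90 tests and are contained in the eight. In each row the six-test rate then lies between the day-90 column and the any-of-8 column.

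**4. Which mismatch matters**

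In these scenarios day-30 mortality exceeds day-28 mortality by 0.7 to 1.7 percentage points. Day-90 mortality exceeds it by 11.8 to 29.1 points (61.8 − 50.0 to 79.1 − 50.0). Day 90 is the materially different endpoint, and the Data collection section does not schedule it.

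**The case against.** The strongest reply has four parts.

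First, a reader might infer that the primary endpoint has no analysis at all, and safety likewise. The document does not support that. Death by day 28 and the proportion of patients with an adverse event are discrete variables, so the general rule can cover both with chi-square or Fisher's exact test. A detailed safety analysis may also properly sit in a statistical analysis plan. This part of the reply stands: the fault is contradictory labels and no lead analysis, not the absence of any analysis.

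Second, only the Cox sentence carries the word primary; the crude tests and the logistic model do not. Read strictly, eight primary tests is an upper count. This also stands. It does not remove the difficulty, because the Cox sentence alone covers two time points, and neither is the declared one.

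Third, a lead test and a multiplicity order are often left to the statistical analysis plan, and the covariates are already fixed in advance, which closes one route to post-hoc choice. That is fair as far as it goes. An unseen plan could choose between the labels, but it could not make the protocol agree with itself.

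Fourth, this is a pilot with a convenience sample, meant to inform a later trial, so error-rate inflation weighs less. That is partly right. But the protocol sets a 0.05 threshold and intends an efficacy comparison, and a pilot that is to supply a mortality rate has to fix the day on which mortality is counted.

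**Conclusion.** The contradiction is certain on the text. 28-day mortality is the declared primary endpoint, the statistical section calls 30- and 90-day survival primary, no analysis is named for day 28, and nothing says which time point or test leads. It should be corrected before any outcome comparison is made.

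The size is less certain. Under no effect, the chance that at least one of eight tests falls below 0.05 is about 14% to 18%, or about 8% to 12% within day 30 alone, against about 5% for one pre-named test. These figures rest on assumed survival curves and covariate effects and on the eight-test reading, and they matter only if the leading result is chosen after the data are seen. A reader might infer inflation of 34% to 40% by treating the tests as separate; their correlation rules that out. Nor does the gap between days 28 and 30 do much harm by itself. The substantive mismatch is day 90.

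**What to change.** In the Statistical analysis section, replace the phrase that makes 30- and 90-day survival primary with one primary analysis: all-cause mortality by day 28 from randomisation, in all randomised patients, as a risk difference with a 95% confidence interval and one named test. Counting from randomisation needs to be stated, because the protocol's Day 0 is tied to the first TPE session, which controls do not have. A single day-28 chi-square test held its level at 4.8% to 5.2% in the simulations above.

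Label the log-rank, Cox and logistic results, and any results at other time points, as supportive, with no separate claim of significance.

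In the Data collection section, record vital status at day 28 for every randomised patient, including those already discharged. Then either add vital status at day 90 or delete the day-90 analyses.

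The cost is that the day-30 and day-90 results lose primary status and that vital status must be checked after discharge. Everything else is a change of wording.
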